**Methods:**

Effectiveness, cost-utility, and neurobiological analyses performed alongside a 12-month RCT. The participants will be 180 adult patients with FMS recruited at the Sant Joan de Déu hospital (St. Boi de Llobregat, Spain), randomly allocated to one of the three study arms: TAU + MBSR vs. TAU + FibroQol vs. TAU. A comprehensive assessment to collect functional, quality of life, distress, costs, and psychological variables will be conducted pre-, post-intervention, and at 12-month post-intervention. Fifty per cent of study participants will be evaluated at pre- and post-treatment using Voxel-Based Morphometry, Diffusion Tensor Imaging, pseudo-continuous Arterial Spin Labeling, and resting state fMRI. A cytokine multiplex kit of high-sensitivity will be applied (cytokines IL-6, IL-8, IL-10 + high-sensitivity CRP test).

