## Methods

### Study design

This RCT protocol was developed following the Standard Protocol Items: Recommendations for Interventional Trials (SPIRIT) [42] and was recorded in the ClinicalTrials.gov trial register in September 2015 (NCT02561416). We designed a 12-month, parallel group, randomised (using a computer-generated randomisation list), single-blind, controlled trial (RCT) with three treatment arms. The Consolidated Standards of Reporting Trials 2010 (CONSORT) [43] and the Consolidated Health Economic Evaluation Reporting Standards (CHEERS) [44] will be followed. The three treatment arms are:TAU + MBSRTAU + FibroQoLTAU

Patients from the three study arms will receive TAU; given that MBSR and FibroQoL were originally developed as complements to usual care, not as substitutes for it. Fifty percent of the participants in each study arm will undergo neurobiological evaluations (neuroimaging and inflammatory markers).

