### Procedure

The potential FMS participants will be screened through an initial telephonic interview by one of the authors ([name]), who will provide a general overview of the study. Subsequently, two highly trained clinical psychologists (not involved with the treatment and blind to group allocation) will make an appointment with those patients who met the inclusion criteria and agreed to participate in the study. The psychologists will check all inclusion/exclusion criteria (both general and additional for the biomarkers study) and will perform all face-to face interviews. As mentioned above, study participants will be randomised to one of the three conditions (i.e., TAU, TAU + MBSR, TAU + FibroQoL). Both MBSR and FibroQoL are conducted in a group format (up to 15 people in each group). To balance the number of participants eligible for the biomarkers sub-study across the three arms, stratified randomisation will be performed. The proportion of eligible participants for the biomarkers evaluation and those only meeting criteria for the general study will be pre-fixed at 1:1 in all samples. Four treatment waves (*N* = 45 each) will be carried out to achieve the required final sample (*N* = 180).

Three-five days after the clinical evaluation, patients assigned to the biomarkers sub-study will be contacted for blood extraction and MRI completion. To minimise circadian variability in immunological markers, all whole blood samples will be collected between 8–9 am. Interventions will be conducted using a parallel design to reduce seasonal variability in the study measures. The participants will be interviewed at baseline, after treatment, and at 12-month follow-up (56 weeks after randomisation). The neuroimaging tests and cytokine measurements will be performed at baseline and after treatment. A flowchart of participants is displayed in Fig. 1.

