We will use the MBSR protocol developed at the University of Massachusetts Medical School, USA. MBSR [47] is intensive, structured training in mindfulness meditation which aims to help patients increase their awareness of the present experience and to relate to their physical and psychological conditions in a more accepting and non-judgmental way. The standard MBSR programme consists of 8 weekly sessions of around 2.5 h each and homework for 45 min a day, 6 days a week, even though several modifications in sessions, homework, and total duration can be observed among distinct courses for various patient populations. MBSR usually has three main components including a “*body scan*”, which involves a gradual sweeping of attention through the entire body from feet to head, focusing non-critically on any sensation or feeling in body regions and using periodic suggestions of breathing awareness and relaxation; “*sitting meditation*” which involves both mindful attention to breathing or on the rising and falling abdomen as well as other perceptions, and a state of non-judgmental awareness of cognitions and of the stream of thoughts and distractions that continuously flow through the mind; and “*Hatha yoga*” practice, which includes breathing exercises, simple stretches, and postures designed to strengthen and relax the musculoskeletal system. In addition to in-class mindfulness exercises, participants are encouraged to engage in home mindfulness practice and attend an all-day intensive mindfulness meditation retreat. The main premise of MBSR is that with repeated training in mindfulness meditation, individuals will eventually learn to be less reactive and judgmental toward their experiences, and more able to recognise, and break free from, habitual and maladaptive patterns of thinking and behaviour. It is important to mention that MBSR is not directed at symptom reduction but more fundamentally towards altering how perceptible mental processes and content are experienced, towards greater awareness, acceptance, and tolerance of the unavoidable vagaries of life, which facilitate enhanced psychological wellbeing, even in the face of continued symptoms. The eight 2 h MBSR sessions (once a week) will be performed in groups (*n* = 15 per group) and will be led by four accredited MBSR instructors (one per group) that have undergone MBSR training, which will enable an analysis of possible instructor effect on the outcomes, as recommended by Öst [48]. A book with MBSR manual and CDs with guided mindfulness practice sessions will be provided to the participants. In addition, we will reinforce MBSR treatment adherence by inviting participants to use a Mindfulness smartphone app developed in 2014 at the University of Zaragoza, Spain. The app has been scientifically validated by the Aragon Institute of Health Sciences. It is the first app that tracks the state of mindfulness and provides feedback on how mindful the person is during mindfulness meditation sessions. It also provides instruction in several mindfulness techniques by means of well-designed videos and audio recordings.

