### Study measures

Study participants will complete the following instruments as part of a paper-and-pencil battery of measures (see Table 3):*Sociodemographic-clinical questionnaire*. The following information will be collected: gender, age, ethnic group, marital status, living arrangements, educational level, employment status, and annual income. Relevant clinical variables, such as family and personal medical history, years of FMS diagnosis and comorbid conditions will also be assessed.

**Table 3 Tab3:** Study periods at which measures and data are collected

Study measures	Baseline	During treatment	2 months	12-months
Demographic information (gender, age, etc.)	X			
History of FMS (years of illness)	X			
Contact details	X			
SCID-I (depression module)	X			
*Screening measures*				
MMSE (cognitive impairment)	X			
*Primary outcome measure*				
FIQR (functional impairment)	X		X	X
*Secondary outcome measures*				
FSDC (fibromyalginess)	X		X	X
HADS (anxiety and depression)	X		X	X
PSS-10 (perceived stress)	X		X	X
MISCI (subjective cognitive impairment)	X		X	X
EQ-5D-5L (quality of life)	X			X
CSRI (health economic evaluation)	X			X
FFMQ^a^ (mindfulness facets)	X		X	X
PCS^a^ (pain catastrophizing)	X		X	X
PIPS^a^ (psychological inflexibility)	X		X	X
SCS-12^a^ (self-compassion)	X		X	X
*Other measures*				
Structural + Functional Neuroimaging data	X		X	
Inflammatory data	X		X	
CEQ (Expectation/Satisfaction with treatment)	X (EXP)		X (SAT)	
PGIC & PSIC (Impression of change)			X	X
Treatment attendance form: Attendance at each scheduled MBSR/FibroQoL session		X		
Log of MBSR and FibroQoL practices		X		
Treatment fidelity (review of video-taped MBSR sessions) & monitoring of adverse events		X	X	X

*CEQ* Credibility/Expectancy Questionnaire, *CSRI* Client Service Receipt Inventory, *EQ-5D-5L* EuroQoL questionnaire, *FFMQ* Five Facet Mindfulness Questionnaire, *FIQR* Revised Fibromyalgia Impact Questionnaire, *FSDC* Fibromyalgia Survey Diagnostic Criteria, *HADS* Hospital Anxiety and Depression Scale, *MISCI* Multidimensional Inventory of Subjective Cognitive Impairment, *MMSE* Mini-Mental State Examination, *PCS* Pain Catastrophizing Scale, *PGIC & PSIC* Patient Global and Specific Impression of Change, respectively, *PIPS* Psychological Inflexibility in Pain Scale, *PSS-10* Perceived Stress Scale, *SCID-I* Structured Clinical Interview for DSM Axis I Disorders, *SCS-12* Self-Compassion Scale

^a^Secondary outcome measures that also considered process variables

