#### Secondary outcome measures and process measures

The *Fibromyalgia Survey Diagnostic Criteria* (FSDC) [59, 60] is a 6-item self-report questionnaire that registers the key symptoms of FMS according to the latest revision of the ACR. It includes assessment through the Widespread Pain Index (WPI) identifying 19 body areas (jaws, shoulders, upper arms, lower arms, hips, upper legs, lower legs, neck, chest, upper back, lower back and abdomen) where pain or tenderness was felt during the previous 7 days (total score 0–19). The Symptom Severity Scale (SS; range from 0–12) includes three major symptoms (fatigue, trouble thinking/remembering and waking up tired or unrefreshed), which is scored from 0 to 3, as well as three additional symptoms (pain or cramps in lower abdomen, depression, headache), which can be coded as present (1) or absent (0). The fibromyalgianess scale is defined as the sum of the WPI items (0–19) and the 6-item SS scale (0–12), so total scores can range from 0 to 31.The *Client Service Receipt Inventory* (CSRI) [61, 62] used for the present project will be designed to collect retrospective data on medication and service receipt: 1. Medication. A profile of the patient’s use of all prescribed medications (analgesics, non-steroidal anti-inflammatories, short- and long-acting opioids, etc.) will be requested, including the name of the drug, the prescriber, the dosage level, the total number of days taking the drug, the total dosage consumed, the reasons for changing the drug, and adherence. 2. Service receipt. We will collect information about emergency services, general medical in-patient hospital admissions and out-patient health care services. Patients will also be asked about type and number of diagnostic tests administered. As shown in Table 3, the CSRI will be administered at baseline and at a 12-month follow-up*; on both occasions, the previous 12 months will be reviewed*.The *EuroQoL-5D questionnaire* (EQ-5D-5L) [63] is a widely used health-related quality of life instrument with a non-disease-specific classification system composed of 2 parts: Part 1 is a self-reported description of health problems classified into five dimensions. Patients mark one of five degrees of severity in each dimension. The time frame is the day of responding. Part 2 records the current subject’s health on a Visual Analogue Scale (VAS); a vertical 10 cm line on which the best and worst imaginable health states score 100 and 0, respectively.The *Hospital Anxiety and Depression Scale* (HADS) [64, 65] was originally developed to quantify the severity of anxiety and depressive symptoms in non-psychiatric hospital patients The HADS includes a total of 14 items that assess anxiety (HADS-A) and depressive (HADS-D) symptoms, with 7 items in each subscale. Each item is answered on a four-point (0-to-3) scale so that possible scores range from 0 to 21 for both anxiety and depressive symptoms, with higher scores indicating greater severity.The *Perceived Stress Scale* (PSS-10) [66] is a 10-item, self-administered instrument that measures the degree to which situations in one’s life are considered stressful. Scores range from 0 to 72. The Spanish version of the PSS-10 has adequate reliability and validity [67].The *Multidimensional Inventory of Subjective Cognitive Impairment* (MISCI) [68] is a 10-item measure of perception of cognitive dysfunction in FMS, developed through classical test theory and item response theory from cognitive functioning item banks that were developed as part of the Patient Reported Outcomes Measurement Information System (PROMIS). The MISCI showed excellent internal reliability, low ceiling/floor effects, and good convergent validity with a similar measure.The *Pain Catastrophising Scale* (PCS) [69, 70] is a 13-item questionnaire derived partially from the Coping Strategies Questionnaire and other descriptions of catastrophising. It has three dimensions: Rumination (tendency to focus excessively on pain sensations), Magnification (tendency to magnify the threat value of pain sensations) and Helplessness (tendency to perceive oneself as unable to control the intensity of pain). The PCS total score and subscale scores are computed as the algebraic sum of ratings made for each item. PCS items are rated in relation to frequency of occurrence on 5-point scales (0 = never ~ 4 = almost always).The *Five Facet Mindfulness Questionnaire* (FFMQ) [71, 72] consists of 39 items that assess five facets of mindfulness. Items are rated on a Likert scale ranging from 1 (never or very rarely true) to 5 (very often or always true). The factors include: *Observing*, including noticing or attending to internal and external experiences such as sensations, thoughts, or emotions. *Describing* refers to labelling internal experiences with words. *Acting with awareness* involves focusing on one’s activities in the here and now as opposed to behaving mechanically. *Non-judging of inner experience* refers to taking a non-evaluative stance toward thoughts and feelings. Finally, *non-reactivity to inner experience* is allowing thoughts and feelings to come and go, without getting caught up in or carried away by them. In a recent online survey answered by 4,986 FMS patients from all 50 US states and 30 countries, the FFMQ subscales was shown to discriminate well among FMS patients self-identified as meditators or non-meditators. Overall, FMS patients with higher mindfulness scores had lower levels of FMS symptom severity as measured with the FIQR [73].The *Self-Compassion Scale-short form* (SCS-12) [74, 75] is a shorter version (12 items) of the SCS (26 items). The SCS was designed to assess overall self-compassion (total score) and components of self-compassion across three dimensions: common humanity, mindfulness and self-kindness. The SCS–SF shows good internal consistency (Cronbach’s α ≥0.86) and very high convergence with the long form of the scale (r ≥0.97).The *Psychological inflexibility in pain scale* (PIPS) [76, 77] is a 12-item scale designed to measure psychological inflexibility in pain patients. The instrument includes two factors: *avoidance* and *cognitive fusion* related to pain. The items consist of different statements that are considered to be related to chronic pain, psychological inflexibility, suffering and disability (coherent with the ACT theory). All the items are rated on a 7-point Likert-type scale that ranges from “1 = never true” to “7 = always true”, with higher scores indicating more psychological inflexibility.

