First, we will use a micro-costing approach, which involves careful specification of training costs, staffing costs, venue overheads, materials, and staff travel. Then, following the International Society for Pharmacoeconomics and Outcomes Research (ISPOR) core recommendations for cost-effectiveness analyses alongside RCTs [91], we will calculate the incremental cost-utility ratios, defined as the difference in mean costs divided by the difference in mean QALYs. As the duration of the study is 12 months, neither costs nor outcomes are subject to discounting. QALYs gained in each evaluation are approximated by using the area under-the-curve technique. To gain insight into the uncertainty around the pooled mean ICUR, we will plot the pooled bootstrapped cost-effect pairs on cost-utility planes. Finally, acceptability curves will be presented which represent the probability that the intervention is cost-effective, given a varying threshold for the willingness to pay for each QALY gained. The robustness of the cost-utility results will also be tested by computing distinct sensitivity analyses. For instance, we will perform a per protocol analysis from which the FMS patients who do not attend at least 6 MBSR or FibroQoL sessions will be excluded.

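### The final assessment carries three different dates, and at the two later ones the CSRI's 12-month look-back leaves the first 4 to 8 weeks of resource use uncollected

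*Protocol article*

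**What the plan says.** The protocol article dates the final visit in several places.

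- Procedure: participants are interviewed "at 12-month follow-up (56 weeks after randomisation".
- Abstract, Methods: assessments are "pre-, post-intervention, and at 12-month post-intervention", and costs and quality of life are among the variables listed for that schedule.
- Study design: "We designed a 12-month, parallel group, randomised".
- Cost-utility analysis: "As the duration of the study is 12 months, neither costs nor outcomes are subject to discounting". Costs are likewise estimated over 12 months of follow-up.
- Table 3: the post-treatment visit is headed 2 months and the last visit 12 months, with no time origin stated.

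The intervention section sets the length of the course: "The eight 2 h MBSR sessions (once a week").

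Table 3 schedules the CSRI and the EQ-5D-5L at baseline and at the final visit only. Of the CSRI, the section on secondary outcome measures says that "on both occasions, the previous 12 months will be reviewed". QALYs are to be obtained as an area under the curve.

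**The concern.** The dates cannot all be right. Two consequences follow, one for the conduct of the trial and one for its data.

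First, this visit supplies the long-term comparison of the primary outcome (FIQR) as well as the economic outcomes, so staff and analysts need one date for it.

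Second, the CSRI rule fixes a look-back of one year from whenever the visit takes place. If the visit falls more than a year after baseline, the look-back does not reach baseline. The baseline CSRI looks backwards from its own date, so it does not cover those weeks either. Resource use that is never asked about cannot be recovered by later analysis. Cost-utility belongs to the first-listed objective, so this is not a peripheral data item.

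**Working it through.** **Inputs.** Final visit at week 56 (Procedure), 12 months post-intervention (Abstract), or 12 months in all (Study design, Cost-utility analysis). Eight weekly sessions (intervention section). CSRI look-back of 12 months (secondary outcome measures). CSRI and EQ-5D-5L at baseline and final visit only (Table 3). The baseline assessment is taken as week 0, the time of randomisation.

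**Step 1: can the 56 weeks be reproduced?** One month is 365.25/12/7 = 4.348 weeks, so 12 months is 52.18 weeks.

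- 12 months from randomisation: 52.18 weeks, which is 3.82 short of 56.
- 8-week course plus 12 months: 8 + 52.18 = 60.18 weeks, which is 4.18 over.
- Eight weekly sessions span 7 weeks from first to last. With session 1 at randomisation, 7 + 52.18 = 59.18 weeks, which is 3.18 over.
- 8 weeks plus twelve four-week months: 8 + 48 = 56. This matches exactly, but the protocol states no such convention.

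In calendar terms 56 weeks is 56/4.348 = 12.9 months.

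**Step 2: where does the follow-up look-back open?** With the visit at week T, it opens at week T − 52.18. The uncovered share of the baseline-to-final interval is (T − 52.18)/T, and the length of that interval in years is T/52.18.

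| Reading | T (weeks) | Look-back opens (week) | Share uncovered | Years from baseline |
|---|---|---|---|---|
| 12 months from randomisation | 52.18 | 0 | 0% | 1.00 |
| Procedure | 56 | 3.82 | 6.8% | 1.07 |
| 12 months after session 8, session 1 at randomisation | 59.18 | 7.00 | 11.8% | 1.13 |
| 12 months after an 8-week course | 60.18 | 8.00 | 13.3% | 1.15 |

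**Step 3: costs against QALYs.** With two EQ-5D-5L measurements the area under the curve is (u0 + u1)/2 × time. If time is the actual interval, QALYs span 1.07 years at week 56 and up to 1.15 years at week 60, against 1.00 year of CSRI costs. If time is the nominal 12 months, the two lengths match at 1.00 year but the periods are offset: the utilities run from baseline, while the CSRI costs start about 4 to 8 weeks later.

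**The case against.** The strongest reply is that this is one visit, loosely labelled. The Procedure itself equates its 12-month follow-up with 56 weeks, and the last column of Table 3 may simply be a visit name. Counting twelve four-week months after the course would reconcile the Procedure with the Abstract. That is possible, but it is not stated. It would still conflict with a 12-month study duration, and a calendar-year look-back would still miss about 4 weeks. The forecast execution dates fit both 56 and 60 weeks, so they do not settle the matter.

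Other parts of the reply do stand, and they rule out stronger readings that a reader might infer.

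- **That half or all of the treatment period is lost.** At week 56, about half (3.82/8 = 48%) is an upper bound, reached only if sessions begin at randomisation. The protocol does not say when they begin, and any wait before session 1 uses up part of the gap. The whole course is missed only if the visit really is dated a full 12 months after it ends, and that date is the very point in dispute.
- **That the QALY time factor is wrong by 7 to 15%.** This arises only if actual dates are used. The Cost-utility analysis treats the study as 12 months, and on that wording the factor is 1.00 year.
- **That the incremental cost is biased, or that substitution of other care is lost.** The gap is the same length in all three arms, and programme costs are micro-costed separately. Incremental cost moves only if the arms differ in other resource use during those weeks, and the protocol gives no figures on that.
- **That nothing at all is known about those weeks.** The Discussion says that patients are asked about treatment changes at post-treatment and follow-up, and that clinicians check the drug history in the chart. This may recover some medication use. The text does not link it to the costing, and it does not cover visits or tests.

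There is also a reason for the present rule: equal 12-month windows at baseline and follow-up give comparable annual costs.

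**Conclusion.** The point holds, and it should be corrected. The final visit is dated inconsistently at about 52, 56 and 59 to 60 weeks. Followed as written, the CSRI rule leaves about 4 weeks of medication, test and service use uncollected if the visit is at week 56, the only timing given in weeks. It leaves about 7 to 8 weeks if the visit is 12 months after the course. There is no gap only at 52 weeks, and then the Procedure and the Abstract are both misstated.

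The figures assume calendar months and a baseline assessment at randomisation; the 59- and 60-week dates also assume that the course starts then. The percentages are shares of elapsed time. They are not estimates of bias in cost or in the cost-utility ratio, whose size and direction cannot be derived from the document.

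**What to change.** 1. Reconcile the Abstract, Study design, Procedure, Table 3 and Cost-utility analysis to one follow-up time counted from randomisation. If it exceeds 12 months, reword the discounting sentence to match.
2. Set the recall period of the follow-up CSRI to run since the baseline assessment.
3. Compute costs and QALYs over the same interval from baseline, and say whether actual or nominal dates are used.
4. Optionally, give the CSRI at the existing post-treatment visit as well, as the Abstract implies.

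Items 1 to 3 need only wording. Their price is a follow-up recall somewhat longer than the 12 months at baseline, by about 4 to 8 weeks if the visit stays at week 56 to 60, so the two windows are no longer equal. Costs per unit of time would remain comparable. Item 4 shortens the recall at the price of some added patient time.
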